### Handling and storage of data and documents

Personal data is handled confidentially and is coded in compliance with the EU General Data Protection Regulation Act (in Dutch: *Uitvoeringswet* AVG, UAVG). Identifying patient information is coded for all study procedures. Only the PI (HK) and one researcher (TK) are allowed to access the keyfile with both participant codes and identifying participant data. The data collected with the actigraph is stored and processed locally on the secure servers of the Amsterdam UMC. The sleep diary is completed by the participants on a paper-and-pencil sheet. This sheet does not include personal information but only the patient’s identification code. The data cannot be traced back to specific participants in reports and publications on the study. Data will be stored at the Department of Medical Psychology of the Amsterdam UMC, location AMC, for 15 years following completion of the project. Data of *Fit after COVID* on the online platform will also be stored for 15 years on a secure server.

### Monitoring and auditing

This study is subject to on-site monitoring in accordance with the quality assurance advice of the Dutch Federation of University Medical Centres regarding research involving human subjects [85]. On-site monitoring is based on the risk classification negligible. The investigator will submit a summary of the progress of the trial to the ethics committee once a year. Information will be provided on the date of inclusion of the first subject, numbers of subjects included, numbers of subjects that have completed the trial, SAEs and amendments.

### Ethics approval and consent to participate

This study was reviewed and approved by the medical ethics committee of the Amsterdam UMC, location AMC (registration nr. 2020_182, NL74828.018.20) and by the local ethics committees of the participating hospitals. The study is registered in the Netherlands Trial Register (NTR) (NL8947). The NTR is updated in case of changes to the study protocol. Written informed consent will be obtained from all participants by the researcher (TK) and the research assistant (DP). All changes in the protocol are sent for approval to the medical ethics committee.

### Participant withdrawal

Participants can leave the study at any time for any reason without any consequences. The reasons are documented. The researcher can withdraw a participant from the study in case of incorrect enrolment. Participants are informed of their possibility to withdraw from the study during the intake and in the information letter. Despite leaving or being withdrawn from the study, treatment can be continued. The investigator, the treating physician, or the treating psychologist can decide to withdraw a participant from the study for urgent (medical) reasons. These reasons are documented. Randomised participants who drop out of the study are not replaced.

### Sample size calculation

The sample size calculation is based on testing the primary hypothesis that CBT leads to a significantly lower mean fatigue severity score (CIS-fatigue) across the first two follow-up assessments (T1 and T2) as compared to care as usual. A difference of 6 points on the CIS-fatigue is considered clinically relevant [38]. Based on previous research we assume a common standard deviation of 12 and correlation coefficients of 0.4 among CIS-fatigue scores assessed at T1 and T2 [27, 31].

With a sample size of 45 in group 1 (CBT) and 45 in group 2 (care as usual), a two-sided test for the time averaged difference between two means in a repeated measures design with a 0.05 significance level has 80% power to detect a difference in means of 6 in a design with 2 repeated measurements when the standard deviation is 12 and the between-level correlation is 0.4. Assuming a conservative dropout of 20%, we will randomise 114 participants, 57 to each condition.

### Statistical analyses

Descriptive statistics (i.e. participant characteristics) will be presented in tables, with separate columns for participants randomised to CBT vs. participants randomised to care as usual. Categorical variables (e.g. sex, relationship status) will be presented in participant numbers (*n*) and percentages (%). Continuous variables (e.g. age, CIS-fatigue baseline score) will be presented in means and standard deviations (SD) or, if appropriate due to skewness of data, as median with its interquartile range. Participant numbers, dropout and reasons for dropout will be presented in the study flow-chart. In all analyses, two-sided *p* values of < 0.05 are considered to indicate statistical significance. All analyses will be conducted in SPSS.

Change in fatigue scores between T0 and T1 for each individual participant will be shown in a figure using the Leeds RCI calculator [86]. This figure will show whether the change was clinically significant and reliable, or reliable only, and if there was no change or a deterioration in fatigue.

The primary study parameter will be analysed according to intention-to-treat, i.e. all randomised participants will be included in the analysis and they are analysed in the group to which they were randomly allocated. The primary hypothesis will be tested using a mixed linear model. The model will include T1 and T2 fatigue severity score as a dependent variable, condition (CBT vs. care as usual), time (T1, T2), condition by time interaction as fixed effects, a random intercept and the fatigue severity score at baseline as covariate. It will be examined if the main effect of condition from the mixed linear model, i.e. the mean difference in CIS-fatigue scores across T1 and T2 while controlling for baseline fatigue, is statistically significant. If the main effect of condition is found to be statistically significant, the statistical significance of the between group differences at the separate time points (T1 and T2) will be interpreted.

Cohen’s d effect sizes will be calculated by dividing the parameter estimate for the mean difference in CIS-fatigue scores between both conditions from the mixed linear model by the pooled standard deviation of both conditions combined. Effect size magnitudes will be interpreted as small (0.2 to 0.5), medium (0.5 to 0.8) and large (greater than 0.8) [87].

To explore the robustness of our findings from the primary analysis, four sensitivity analyses will be conducted. First, per protocol analysis will be conducted. Treatment completion will be operationalized in two ways, i.e. by including (a) participants who have filled out the treatment goals and opened the standard modules of the intervention and (b) participants who have completed the intervention according their therapist.

Second, as the primary outcome consists of the mean CIS-fatigue score across T1 and T2, the extent to which our result would change if based on a single time point will be explored. Therefore, the analysis with the CIS-fatigue score at T1 as a dependent variable and with the CIS-fatigue score at T2 as a dependent variable adjusted for CIS-fatigue score at baseline using analysis of covariance will be repeated. For each of the time points Cohen’s d effect sizes will be calculated.

Third, the extent to which dyspnoea at T0, disease severity, time since diagnosis of COVID-19, age and sex have an impact on the primary outcome will be explored, and whether this impact differs between CBT and care as usual. These analyses will be conducted by including these variables and their interaction-terms with condition as covariates in the mixed linear models.

Fourth, missing values will be replaced with multiple imputation using chained equations and the data will be reanalysed. The imputation model will include all baseline sociodemographic and clinical characteristics assessed at baseline and follow-up measurements. A total of five data sets will be imputed and pooled according to Rubin’s rule.

Secondary outcomes will also be analysed according to intention-to-treat. For T1 and T2, it will be determined if there is a clinical meaningful improvement in fatigue, defined as a RCI [84] of more than 1.96 and a decrease of the fatigue level to a normal range (i.e. a score of < 35 on the CIS-fatigue). For secondary outcomes that are dichotomous, separate logistic regression analysis will be done for T1 and T2. For secondary outcomes that are continuous (i.e. physical functioning, work and social adjustment, somatic symptoms, cognitive symptoms), differences between CBT and care as usual will be analysed using mixed linear models as described above.

For the long-term follow-up (T3) examining the course of fatigue over time within the CBT group, linear mixed model analyses will be applied, where the depended measure CIS-fatigue is assessed at T0, T1, T2 and T3.

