### Randomisation

Allocation of participants to either CBT or care as usual is stratified based on (1) illness severity during the acute stage of COVID-19 (no admission to hospital; admitted to hospital, not on the intensive care unit (ICU); ICU during hospitalisation) and (2) dyspnoea based on the Medical Research Council (MRC) [59] score (< 3 vs. ≥ 3). This is because dyspnoea might influence the response to CBT by interfering with the graded activity module. A web-based randomisation programme in Castor EDC [60] is used to generate the randomisation sequence. The allocation ratio is 1:1. Block-randomisation with randomly selected block sizes (i.e. 2, 4 or 6) is used. The randomisation is performed by a research assistant in the presence of the participant who is on the phone. The research assistant, the researcher and the participants are blinded to the allocation sequence. Due to the nature of the intervention, blinding to allocation is not feasible. Data will be analysed by an independent statistician using a data file which is blinded for treatment allocation.

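### The primary mixed model leaves out both randomisation strata, so its standard error may be somewhat too large; the cost is a small loss of efficiency, not bias

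*Protocol article*

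**What the plan says.** **Randomisation.** "Allocation of participants to either CBT or care as usual is stratified based on (1) illness severity during the acute stage of COVID-19", with levels for no admission, hospital ward and ICU, and also on MRC dyspnoea score (below 3, or 3 and above). Blocks of 2, 4 or 6 are used. The reason given for dyspnoea is that it could interfere with the graded activity module and so change how participants respond to CBT.

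**Statistical analyses, primary model.** The dependent variable is CIS-fatigue at T1 and T2. The listed terms are condition, time and "condition by time interaction as fixed effects, a random intercept and the fatigue severity score at baseline as covariate". The tested effect is described as the mean difference across T1 and T2 controlling for baseline fatigue. The covariate set is therefore fixed in the text, and neither stratification factor is in it. The continuous secondary outcomes use the same model.

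**Statistical analyses, third sensitivity analysis.** Dyspnoea at T0, disease severity, time since diagnosis, age and sex are explored "by including these variables and their interaction-terms with condition as covariates in the mixed linear models". This is the only place where the stratification factors enter a model.

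**The concern.** Stratified blocks remove most of the chance imbalance between arms on the stratification factors, so the treatment difference varies less from trial to trial than it would under simple randomisation. A model without those factors does not register this. It leaves the between-stratum variation in the error term and reports the standard error of an unstratified trial. If the strata predict the outcome, the confidence interval is wider than it need be and the test rejects less often than 5% under the null.

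What is at stake is precision that the design has already secured. The omission is written into the model specification, so it is not simply a detail left to an analysis plan that is not shown.

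**Working it through.** **Inputs from Sample size calculation.** The calculation uses "a two-sided test for the time averaged difference between two means in a repeated measures design with a 0.05 significance level"; it "has 80% power to detect a difference in means of 6 in a design with 2 repeated measurements"; the SD and correlation are a "common standard deviation of 12 and correlation coefficients of 0.4 among CIS-fatigue scores assessed at T1 and T2"; there are 45 evaluable participants per arm and 57 per arm randomised.

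**Assumed input.** R² is the share of the variance of the T1/T2 mean, left after baseline CIS-fatigue, that the strata explain. The article gives no value. The range used is 0 to 20%.

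**1. Reproduce the plan's figure.**
- SD of the mean of two measurements: 12 × √((1 + 0.4)/2) = 10.04.
- Standard error with 45 per arm: 10.04 × √(2/45) = 2.117.
- Power for a 6-point difference, by noncentral t on 88 df: 80.06%. With 44 per arm it is 79.2%, so 45 is the t-based answer.
- With 20% dropout: 45/0.8 = 56.25, rounded up to 57 per arm, or 114 in total. The stated figures reproduce, and they assume no covariate adjustment.

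**2. Type I error without the strata.** With perfect balance within strata, the true standard error is 2.117 × √(1 − R²) while the reported one stays at about 2.117. Hence α = 2 × [1 − Φ(1.96/√(1 − R²))].

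**3. Power without the strata.** Stratified allocation helps the unadjusted test too. The critical difference is 1.987 × 2.117 = 4.206, so power ≈ 1 − Φ((4.206 − 6)/(2.117 × √(1 − R²))). For example, at R² = 10% the true standard error is 2.008 and power is 1 − Φ(−0.893) = 81.4%.

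**4. Power with the strata.** This is noncentral t with the SD multiplied by √(1 − R²) and 3 df spent (two for severity, one for dyspnoea).

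| Assumed R² | Type I error, no strata | Power, no strata | Power, with strata |
|---|---|---|---|
| 0 | 5.0% | 80.2% | 80.0% |
| 2% | 4.8% | 80.4% | 80.8% |
| 5% | 4.4% | 80.8% | 82.0% |
| 10% | 3.9% | 81.4% | 84.0% |

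The third column is a normal approximation and runs about 0.1 point high (80.2% against 80.06% at R² = 0). Allowing for that, the gain is roughly 0.5, 1.3 and 2.6 points.

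**5. Simulation with realistic imbalance.** Permuted blocks of 2, 4 or 6 in six strata, 90 participants, 6,000 runs per setting, fitted to participant means. Stratum shares were assumed: 80/15/5% for severity and 30% with MRC 3 or above.

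| R² | Type I error, no strata | Reported SE, no strata (null runs) | Actual SE, no strata (null runs) | Power, no strata | Power, with strata |
|---|---|---|---|---|---|
| 0 | 4.8% | 2.11 | 2.11 | 80.1% | 80.0% |
| 2% | 4.6% | 2.11 | 2.08 | 80.4% | 80.5% |
| 5% | 4.4% | 2.11 | 2.06 | 79.9% | 81.4% |
| 10% | 4.3% | 2.11 | 2.04 | 80.5% | 83.2% |
| 20% | 3.2% | 2.11 | 1.94 | 81.7% | 87.2% |

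With the strata in the model, type I error was 4.7–5.0% throughout. Bias without the strata was negligible (at most 0.04 points). Monte Carlo error is about √(0.05 × 0.95/6000) = 0.3 points for type I error and √(0.8 × 0.2/6000) = 0.5 points for power, so the rows for 2% and 5% show direction more than exact size. At 10%, imperfect balance gives 4.3% where the formula gives 3.9%.

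**The case against.** The strongest reply is that nothing the article claims becomes false. The estimate is unbiased, type I error is not inflated, the intention-to-treat analysis is intact, and the 80% power was derived without covariates and is met. All of this stands.

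The size of the loss is also unknown. A reader might take the reason given for stratifying on dyspnoea as evidence that dyspnoea predicts fatigue. The article does not support that: it says dyspnoea might change the response to CBT, which is effect modification, whereas the efficiency argument needs prediction of the outcome in both arms. A reader might also compare adjusted power of up to 84% with the planned 80% and credit the whole difference to adjustment. That comparison is wrong, because stratified allocation raises the unadjusted test as well, to about 81.4% at R² = 10%.

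On the third sensitivity analysis, a reader might infer one joint model in which the condition coefficient cannot be an average effect. The text does not say whether the variables enter together or one at a time, and with centring or marginal means an average effect could be recovered. What stands against relying on this analysis is narrower: it is exploratory, and it plans no strata-adjusted main effect of condition.

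Finally, the argument does not carry over to the dichotomous secondary outcomes. In logistic regression, adding covariates changes the odds ratio being estimated, and a sparse ICU level could cause separation.

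**Conclusion.** The point holds as a mismatch between design and analysis with a modest efficiency cost. That the strata are omitted from the primary model is certain from the text. The direction is also clear: where the strata are prognostic beyond baseline CIS-fatigue, the reported standard error is too large and the test is conservative.

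The size depends on an R² that the article does not give. At 2%, 5% and 10%, type I error is about 4.6–4.8%, 4.4% and 3.9–4.3%, and the power forgone is roughly 0.5, 1.3 and 2.6 points. At 20% the simulation puts the loss at 5.5 points (81.7% against 87.2%). At 0 there is no loss. These figures use the sample size basis of SD 12 and correlation 0.4 with 45 per arm, and do not credit the baseline covariate that the primary model will contain.

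The article does not support reading this as a threat to validity or as a shortfall against the planned power.

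**What to change.** Before unblinding, make three changes in the analysis section or the analysis plan:

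- Add acute illness severity (no admission, ward, ICU) and MRC category (below 3, or 3 and above) as fixed main effects to the primary mixed model and to the mixed models for the continuous secondary outcomes.
- State in advance how a sparse level is pooled, for example ward and ICU combined below a set count, judged on stratum totals without sight of allocation or outcome.
- Keep the interactions with condition in the exploratory third sensitivity analysis.

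Leave the logistic models outside this change unless the sponsor first states whether a conditional or a marginal odds ratio is intended.

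The cost is a short text change and at most 3 degrees of freedom. At R² = 0, power moves from 80.06% to 80.03%. No new data are needed, because both factors must be known for every participant at randomisation.

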### Therapist training

Six therapists working at the participating hospitals completed a 4-day training programme provided by a senior clinical psychologist (HK). The training consists of discussing each treatment module and practising the interventions in role-playing with simulation patients, being professional actors. An introduction to the online platform, exercises in writing e-mails and giving online feedback are part of the training. Five therapists working at the Expert Centre for Chronic Fatigue (ECCF) of the Amsterdam UMC were already trained in the protocol for CBT for CFS, but followed an additional 2-hour training programme on COVID-19-specific issues.

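### Clustering by therapist in the CBT arm is allowed for in neither the primary model, the sensitivity analyses nor the sample size; if therapists differ, the test leans towards CBT

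*Protocol article*

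**What the plan says.** Under Intervention, the Protocol article says that CBT is delivered by cognitive behavioural therapists and opens with an intake by the assigned therapist. Therapist training describes two groups: "Six therapists working at the participating hospitals completed a 4-day training programme" and "Five therapists working at the Expert Centre for Chronic Fatigue (ECCF) of the Amsterdam UMC were already trained"; the second group added a 2-hour course on COVID-19-specific issues. That makes 6 + 5 = 11 trained therapists. The article does not say how many of them treat trial participants, or with what caseloads. Under Care as usual there is no study therapist.

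Statistical analyses lists the primary model term by term: condition, time and their interaction as fixed effects, then "a random intercept and the fatigue severity score at baseline as covariate". The four sensitivity analyses are per protocol, single time points, covariates with interactions, and multiple imputation. The continuous secondary outcomes use the same form of model. The sample size takes an SD of 12 and a T1–T2 correlation of 0.4, and claims that the trial with 45 per arm "has 80% power to detect a difference in means of 6 in a design with 2 repeated measurements". Therapist variation is addressed only operationally, by bi-weekly supervision (Adherence and treatment integrity).

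**The concern.** Patients who share a therapist may have outcomes more alike than patients who do not. This can happen in the CBT arm only, which makes the design partially nested. The one random intercept has to carry the correlation between a participant's T1 and T2 scores, so nothing is left to carry variance between therapists.

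If that variance is above zero, the model understates the variance of the CBT mean. The interval is then too narrow and the p value too small, so a false claim of benefit is more likely than the nominal level implies. The stated power is also calculated as if CBT participants were independent. Because the model is spelled out in full and the sensitivity analyses are counted, this is a feature of the stated plan and not a detail that the article leaves open.

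**Working it through.** **Inputs from Sample size calculation:** difference 6, SD 12, T1–T2 correlation 0.4, two-sided 5%, 45 per arm evaluable, 57 per arm randomised. **From Therapist training:** 11 therapists trained. **Assumptions:** all 11 are active with equal caseloads; the single-visit therapist ICC is 0.02, 0.05 or 0.10; a therapist's effect is the same at T1 and T2.

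**1. The plan's own figure.** Variance of a participant's T1/T2 mean = 12² × (1 + 0.4)/2 = 100.8, so SD = 10.04. The standard error of the difference is √(2 × 100.8/45) = 2.117. A noncentral t with 88 df gives power 80.06%. Then 45/0.8 = 56.25, rounded up to 57 per arm, 114 in all. The figures reproduce under independence, with almost no slack.

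**2. ICC on the scale of the two-visit mean.** A stable therapist effect does not average out over visits, whereas part of the participant variance does. The share of therapist variance is therefore ICC × 144/100.8 = ICC/0.7, which is 0.029, 0.071 and 0.143.

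**3. Clustering in one arm.** Caseload k = 45/11 = 4.09, or 57/11 = 5.18. Design effect in the CBT arm: DE = 1 + (k − 1) × ICC/0.7. Variance ratio for the difference: R = (1 + DE)/2. Type I error when therapist is ignored: 2 × [1 − Φ(1.96/√R)]. Power uses the noncentral t (88 df) with standard error 2.117 × √R.

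| Single-visit ICC | DE (45) | √R (45) | Type I, 45 per arm | Type I, 57 per arm | Power, 45 per arm |
|---|---|---|---|---|---|
| 0 | 1.00 | 1.00 | 5.0% | 5.0% | 80.1% |
| 0.02 | 1.09 | 1.02 | 5.5% | 5.7% | 78.3% |
| 0.05 | 1.22 | 1.05 | 6.3% | 6.8% | 75.8% |
| 0.10 | 1.44 | 1.10 | 7.6% | 8.6% | 71.8% |

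The inflation is larger at 57 because each therapist then has more participants.

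**4. Uneven caseloads.** With a coefficient of variation of 0.5 (assumed), k is replaced by k × (1 + 0.5²) = 5.11 at 45 per arm. At ICC 0.05, type I error is then 6.7% and power 74.5%. Fewer active therapists act in the same direction.

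**5. Credit for the baseline covariate.** With an assumed baseline-to-follow-up correlation r, participant variance falls to 100.8 − r² × 144. For r = 0.3 this is 87.84. At ICC 0.05 the therapist variance is 0.05 × 144 = 7.2, so the CBT arm has 87.84 + 7.2 × 3.09 = 110.1. The standard error is √((87.84 + 110.1)/45) = 2.097 and power is about 81%. But R = (87.84 + 110.1)/(2 × 87.84) = 1.127, so type I error is about 6.5%. Power is restored; the error rate is not.

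**The case against.** A reader might infer that the standard error is definitely too small, that 80% power is reached only with no therapist effect at all, or that the primary model is invalid and must be replaced. The documents do not support any of these.

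- **Size unknown.** No ICC is given. Different training routes do not show that outcomes differ, and standard modules with fixed cut-offs and supervision of every case may keep therapist variance low. At ICC 0.02 the true standard error is only about 2% above the model's. This stands, so the result must be put conditionally.
- **Power.** The zero-effect reading fits the sample size calculation as written, but not the planned analysis. That analysis adjusts for baseline, and dropout below 20% would also add power. This stands for power only.
- **Stability over time.** T2 is six months after T1. If the effect were present at T1 and gone by T2, a T1 ICC of 0.05 would contribute 0.05 × 144/4 = 1.8, or 0.018 of 100.8. Type I error would be about 5.3% at 45 per arm and power about 79%. Stability is an assumption.
- **Number of therapists.** Eleven is a count of those trained. Fewer would worsen the effect.
- **Inference target.** If conclusions are meant for these therapists alone, a participant-level model is defensible. But the Discussion looks to wide implementation, which points beyond them.
- **Small clusters.** About eleven clusters of four or five estimate the variance poorly, and REML may return zero. This argues for a sensitivity analysis over a new primary model.

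**Conclusion.** The point holds in conditional form. CBT participants are nested in therapists, and no part of the stated analysis or sample size allows for it. Any positive therapist ICC makes the test anti-conservative in favour of CBT. Over assumed single-visit ICCs of 0.02 to 0.10, the error rate is roughly 5.5% to 7.6% at the 45 per arm used for power, and 5.7% to 8.6% if all 57 are analysed. These figures rest on eleven equal caseloads and an effect that is stable over T1 and T2.

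The loss of power, from 80% to between about 78% and 72%, is the weaker part, because baseline adjustment may offset it. This is a modest weakness that should be corrected. It would matter most if the primary p value fell close to 0.05.

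**What to change.** 1. Pre-specify a fifth sensitivity analysis of the primary outcome: the same model plus a therapist random effect in the CBT arm only, with care-as-usual participants as singletons, fitted by REML with small-sample degrees of freedom. Define therapist as the one assigned, and say how a change of therapist is handled. Report the therapist variance, the number of active therapists and their caseloads.
2. Add to Sample size calculation that the 80% assumes no therapist clustering and takes no credit for baseline adjustment, with the range of power over plausible ICCs.

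The cost is mainly wording. Therapists already register each contact, so their identity should be available. At the time of the article recruitment was still open, which left time to fix this before analysis. The downsides are a slightly wider interval in that analysis and an imprecise, possibly zero, therapist variance. One practical point: the statistician is to work on a file blinded to allocation, and a therapist code would reveal the CBT arm. The analysis should therefore be run after the blinded primary analysis is complete.

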Research on other medical conditions has indeed shown that cognitive behavioural variables, like a disrupted sleep-wake pattern, low or unevenly distributed level of activity, or dysfunctional fatigue-related beliefs, can explain the persistence of fatigue [18, 22]. These factors seem transdiagnostic, i.e. they have been found to perpetuate fatigue across different diseases and long-term medical conditions [23, 24]. We expect that the same factors also play a role in fatigue following COVID-19. These cognitive behavioural perpetuating factors can be addressed in cognitive behavioural therapy (CBT) [25]. Previous research into post-infectious fatigue following Q-fever [26] and chronic fatigue in other conditions [27–30] has shown that CBT can lead to a significant reduction in fatigue severity and disability. Effect sizes are moderate to large with a substantial proportion of patients showing clinically relevant improvement in fatigue directly following treatment [26, 27, 29, 31]. We assume that addressing the transdiagnostic cognitive behavioural perpetuating factors may also lead to a reduction of severe fatigue following COVID-19. Data on long-term outcomes after CBT are mixed with some studies showing maintenance of treatment effects [32], while others show partial maintenance of treatment effects with relapse in a supgroup of patients [33–35].

The efficacy of CBT for fatigue has mostly been tested in populations with a long duration of fatigue and impairments, often several years. There is evidence that a long symptom duration is associated with a less favourable outcome of CBT [36]. Thus early intervention may help to prevent severe fatigue becoming chronic. On the other hand, in glandular fever, considerable spontaneous recovery from acute fatigue in the first three months after an infection [37] is observed. Three months following the acute phase of COVID-19 may therefore be the optimum time point to start an intervention.

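### The random-intercept model assumes equal variance at T1 and T2: harmless for the averaged primary test, but it miscalibrates the T1 and T2 standard errors if the spreads differ

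*Protocol article*

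**What the plan says.** The primary model (Protocol article, Statistical analyses) takes the T1 and T2 CIS-fatigue scores as the outcome. Its fixed effects are "condition (CBT vs. care as usual), time (T1, T2), condition by time interaction as fixed effects", to which it adds "a random intercept and the fatigue severity score at baseline as covariate". No residual covariance structure is named.

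The primary test is the main effect of condition, that is, whether "the mean difference in CIS-fatigue scores across T1 and T2 while controlling for baseline fatigue, is statistically significant". Only if that test succeeds does the plan go on to the single visits: "the statistical significance of the between group differences at the separate time points (T1 and T2) will be interpreted".

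Two further statements in the same section matter. The second sensitivity analysis looks at T1 and T2 one at a time, each "adjusted for CIS-fatigue score at baseline using analysis of covariance will be repeated". And the continuous secondary outcomes reuse the primary mixed model.

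For planning, the Sample size calculation section says "we assume a common standard deviation of 12 and correlation coefficients of 0.4 among CIS-fatigue scores assessed at T1 and T2". No SD is given for either visit alone.

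**The concern.** With two visits, a random intercept plus a single residual variance is compound symmetry: one variance shared by T1 and T2, and one covariance. If the true spreads differ, the model uses their average at both visits. The visit with less spread then gets a standard error that is too large, and the visit with more spread gets one that is too small.

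This matters because the plan interprets the difference at each visit as part of its main strategy. T2 is where the reader learns whether the effect lasts six months beyond the end of treatment. A confidence interval there that is too narrow or too wide bears directly on that question. The same model serves physical functioning, work and social adjustment, somatic symptoms and concentration, for which no separate analysis by visit is stated.

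**Working it through.** **Inputs from the article.** Common SD 12, T1–T2 correlation 0.4, difference 6, two-sided alpha 0.05, 45 evaluable per arm, 57 per arm randomised.

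**Assumed inputs.** Visit-specific SDs, read as the spread left after baseline adjustment. The pairs 12/12, 11/13, 10/13, 10/14 and 9/15 (T1/T2) show a range.

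**Step 1. The plan's own figure.** The SD of the two-visit mean is 12 × √((1 + 0.4)/2) = 10.04. Then n per arm = 2 × (1.960 + 0.842)² × 10.04² / 6² ≈ 44. With 45 per arm, power is 80.9% (normal) or 80.1% (t, 88 df), which agrees with the statement that the design "has 80% power to detect a difference in means of 6". Dropout: 45/0.8 = 56.25, rounded up to 57 per arm, 114 in total. The stated sample size reproduces.

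**Step 2. The averaged contrast.** The true variance of a participant's two-visit mean is (s₁² + s₂² + 2ρs₁s₂)/4. Compound symmetry replaces both variances by (s₁² + s₂²)/2 and leaves the sum unchanged. At 11/13: (121 + 169 + 2 × 0.4 × 143)/4 = 101.1 under the truth, and (145 + 145 + 114.4)/4 = 101.1 under the model. With complete data the primary test therefore has the right standard error.

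**Step 3. The visit-specific contrasts.** The model SD at each visit is p = √((s₁² + s₂²)/2). The ratio of model to true standard error is p/s at that visit. The actual level of a nominal 5% test, taken on its own, is 2 × (1 − Φ(1.96 × p/s)).

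| SD at T1/T2 | p | SE ratio T1 | SE ratio T2 | Level T1 | Level T2 |
|---|---|---|---|---|---|
| 12/12 | 12.00 | 1.000 | 1.000 | 0.050 | 0.050 |
| 11/13 | 12.04 | 1.095 | 0.926 | 0.032 | 0.070 |
| 10/13 | 11.60 | 1.160 | 0.892 | 0.023 | 0.080 |
| 10/14 | 12.17 | 1.217 | 0.869 | 0.017 | 0.089 |
| 9/15 | 12.37 | 1.374 | 0.825 | 0.007 | 0.106 |

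**Step 4. Check by simulation.** REML compound-symmetry fits with 57 per arm, correlation 0.4, no effect, 0% or 20% dropout, and 3,000 runs per setting:

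- At 11/13 the level was 0.032–0.036 at T1 and 0.068–0.071 at T2.
- At 10/14 it was 0.017–0.018 at T1 and 0.089–0.093 at T2.
- The main-effect test stayed at 0.044–0.058 in all five settings.
- Separate baseline-adjusted covariance analyses stayed at 0.044–0.057 at both visits.

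The Monte Carlo standard error near 0.05 is √(0.05 × 0.95/3000) = 0.004, so the last two ranges are compatible with 5%.

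**Step 5. With the gate applied.** The levels in Steps 3 and 4 ignore the condition that the main effect must first be significant. Simulations of the gated procedure (45 per arm, correlation 0.4) gave false T2 claims as follows:

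- No effect at either visit: 3.3% of trials at 11/13 (7.2% ungated) and 3.8% at 10/14 (8.7% ungated).
- A true T1 effect of 6 to 12 points and none at T2: about 3.5–3.7% at 11/13 and 4.4–4.6% at 10/14.
- For comparison, at a T1 effect of 12, using each visit's own variance gave 2.6% (11/13) and 2.5% (10/14).

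**The case against.** The case against raising this is substantial, and most of it stands.

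- **Unequal spread is assumed.** The article states one common SD of 12. A reader might infer from the Background section that the trial expects relapse in some participants and hence a wider T2. That section reports mixed results of earlier studies: some with maintained effects, others with "partial maintenance of treatment effects with relapse" in part of the sample. It states no expectation for this trial and says nothing about variance. On a scale bounded at 8 and 56, the direction of any change in spread is not obvious.
- **A random intercept does not by itself force equal variances.** It does so with a homogeneous residual. The residual structure is not named and may be settled in an analysis plan that is not shown. The point is therefore about the consequence of the stated random intercept under the usual default, not about an omission.
- **The gate limits false claims.** A reader might take the 7% to 9% levels at T2 as the plan's error rates. They are not, because the visit tests are never run on their own; with the gate, the rate stayed below 5% in the settings simulated. Two limits remain. The gate protects less as the T1 effect grows, since it then opens nearly always. And it does nothing for the standard errors and confidence intervals themselves.
- **Valid visit-specific analyses are already planned.** The separate covariance analyses estimate their own variances. They are, however, a sensitivity analysis, are stated for CIS-fatigue only, and do not use T1 data for participants whose T2 score is missing.
- **The secondary objectives on continuous outcomes are also averages over T1 and T2.** For those outcomes the exposure is therefore limited to any visit-specific difference that is reported.

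**Conclusion.** The point holds as a minor improvement to a stated modelling choice. Under the usual homogeneous residual, the T1 and T2 differences from the primary model have correct standard errors only if the two spreads are equal. At assumed SDs of 11/13 the error is about 10% too large at T1 and 7% too small at T2; at 10/14 it is about 22% and 13%; at 12/12 it is nil. The averaged primary test is essentially unaffected throughout, and the sample size stands.

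The documents do not support a claim that the spreads will differ, that the T2 conclusion will be wrong, or that the trial's false-claim rate exceeds 5%. What remains is that the visit-specific intervals depend on an assumption the analysis does not need.

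**What to change.** In the mixed model, replace the random intercept with an unstructured 2 × 2 residual covariance for T1 and T2: the REPEATED statement in SPSS, fitted by REML, with Satterthwaite or Kenward-Roger degrees of freedom. Keep the fixed effects, the baseline covariate, the main-effect test and the gate as they are. Apply the same structure to the continuous secondary outcomes. If an analysis plan already allows visit-specific residual variances, a sentence saying so is enough.

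The cost is one extra variance parameter and a small change of syntax. Nothing material is lost if the two spreads turn out equal, and no change to the sample size is needed.
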